### Interim analyses {21b}

An interim analysis for efficacy of the primary endpoint will be done when 50% of planned sample size is assessed at 6 months. And it will give a recommendation whether the study should be continued or stopped.

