### Outcomes {12}

In this trial, the outcomes will be developed according to the standard clinical endpoint of endovascular aortic repair [17]. The primary outcome will be the all-cause mortality (30 days). The secondary outcomes will include incidence of secondary intervention (30 days, 6 months, 1 year), incidence of endoleak (30 days, 6 months, 1 year), incidence of major adverse events (MAE) (i.e., immediate procedural success and complications) (30 days, 6 months, 1 year), immediate technical success rate, and all-cause mortality (6 months, 1 year). All-cause mortality is the annual number of deaths in a given group per the population in that group. Endoleak was assessed by DSA angiography during surgery and by CTA and DUS after surgery. We recommend re-intervening to achieve a proper seal in patients with type I or type III endoleaks following TEVAR according 2024 ESC Guidelines [18]. We recommend to perform 30-day imaging after TEVAR, by CTA and DUS, to assess the success of intervention. A secondary intervention will be performed if necessary, based on the follow-up results and the patient’s condition.

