### Sample size {14}

The power of the trial is calculated as two co-primary endpoints, sharing a combined *α*-level of 0.05. According to the literature, cumulative 30-day all-cause mortality was similar in both groups: 3.8% [8]. An equal (1:1) equivalence design was used, with *α* = 0.05 (two-sided), *β* = 0.20 (two-sided), Δ = 10%, from which the sample size *n* was estimated. In accordance with the design of the trial and the primary efficacy outcome measures, the sample size was estimated using the following formula:$$n=\frac{\pi_t\times\;\left(1-\pi_t\right)\;+\;\pi_c\;\times\;\left(1-\pi_c\right)}{\left(\mathit\triangle\mathit\;\mathit-\mathit\;\mathit{\left|{\pi_t-\pi_c}\right|}\right)^2}\times\left(\mu_{\mathit a\mathit/\mathit2}\mathit+\mu_{\mathit\beta}\right)^2$$

A minimum of 154 patients (77 per group) will need to be recruited. However, considering a potential dropout rate of 10%, combined with the low probability of adverse events in this trial, the total sample size was expanded to 170 patients.

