## Statistical methods

### Statistical methods for primary and secondary outcomes {20a}

Baseline characteristics and clinical outcomes will be expressed as numbers (percentages) for categorical variables and mean ± standard deviation for continuous variables. The chi-square test or Fisher’s exact test will be used to analyze categorical variables, and the independent *t*-test or the Wilcoxon signed-rank test will be adopted to analyze continuous variables. The Kaplan–Meier method will be performed to generate survival curves, and the log-rank analysis will be used to compare the differences between survival curves. Multivariate Cox regression adjusted by centers will be applied to calculate the hazard ratio risk. *P* < 0.05 will be considered to indicate statistical significance.

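### The interim efficacy look can lead to a stop, but the article states only a flat P < 0.05 and spends the full alpha at one look; its 6-month trigger also does not match the 30-day endpoint

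*Protocol article*

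**What the plan says.** Interim analyses {21b} consists of two sentences. The first reads "An interim analysis for efficacy of the primary endpoint will be done when 50% of planned sample size is assessed at 6 months"; the second says that "it will give a recommendation whether the study should be continued or stopped". No boundary or adjusted final level is given there.

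Outcomes {12} fixes the endpoint: "The primary outcome will be the all-cause mortality (30 days"). Mortality at 6 months is listed among the secondary outcomes: "immediate technical success rate, and all-cause mortality (6 months, 1 year").

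Statistical methods {20a} sets one threshold, P < 0.05, which "will be considered to indicate statistical significance". Methods for additional analyses {20b} repeats it. Neither section makes an exception for the interim or the final analysis.

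Sample size {14} uses a fixed-sample formula with two-sided alpha 0.05, beta 0.20 and a 10-point margin. Its only remark on dividing alpha concerns endpoints, not looks: "The power of the trial is calculated as two co-primary endpoints, sharing a combined *α*-level of 0.05". Section {20c} makes the confirmatory claim one of non-inferiority of extracorporeal to in situ fenestration, required in both the ITT and PP sets.

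**The concern.** There are two separate problems.

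**Error control.** An efficacy look at the primary endpoint that can end the trial is a second chance to succeed. If both looks use the stated threshold and the final analysis already uses all of the alpha, the overall error exceeds the stated level. Few deaths are expected and the margin is 10 points, so an early success would be common under the planning assumptions and would rest on very few events. Non-inferiority is the trial's confirmatory claim, so this is the error rate that matters.

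**Timing.** A look at 30-day mortality does not need 6-month data. A reader cannot tell whether the look tests 30-day mortality about five months after the data are complete, or 6-month mortality, which is secondary.

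**Working it through.** **Inputs.** Mortality 3.8% in both arms, margin 0.10, two-sided alpha 0.05, 77 per group, 170 in total (Sample size {14}); 1:1 allocation (Trial design {8}); look at 50%, which is 85 patients ({21b}); P < 0.05 ({20a}, {20b}). Assumptions: two-sided P < 0.05 corresponds to one-sided 0.025 for non-inferiority, the threshold applies at both looks, and extracorporeal fenestration is the tested arm ({20c}).

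**1. The plan's own sample size.**
n = [0.038 × 0.962 + 0.038 × 0.962] / 0.10² × (z_α/2 + z_β)² = 7.3112 × (z_α/2 + z_β)²

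- z = 1.960 and 1.2816 (beta halved): 7.3112 × 10.508 = 76.8, so 77 per group and 154 in total. This is the stated figure.
- z = 1.960 and 0.8416 (beta not halved): 57.4, so 58 per group.
- Alpha halved over two endpoints: 70 (beta not halved) or 91 (beta halved) per group.

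Of these variants, only the full two-sided 0.05 at one analysis (with beta halved) gives 77. Nothing is set aside for an interim.

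**2. Two looks at 1.96, normal theory.** The correlation between looks at 50% and 100% information is √0.5 = 0.707.
One-sided: 1 − Φ₂(1.96, 1.96; 0.707) = 0.0416, against 0.025. Two-sided: 0.083, against 0.05.

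**3. Exact binomial error for non-inferiority.** True rates 13.8% and 3.8% (at the margin), final analysis at 85 per arm, interim at 42 + 42 or 43 + 42:

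| Test | One look | Two looks at 1.96 |
|---|---|---|
| Score | 2.4% | 3.7-3.9% |
| Wald | 3.4% | 6.0-6.4% |

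The Wald test is already above 2.5% with one look, so only the rise from 3.4% is due to the interim.

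**4. Chance of an early non-inferiority result, both arms at 3.8%, 84 or 85 patients counted.**

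- Score: 41% at 42 vs 42, and 51% at 43 vs 42. The jump comes from a single outcome. One death in each arm gives z = −1.93 at 42 vs 42 (fails) and −1.97 at 43 vs 42 (passes).
- Wald: 65-66%.

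**5. Events behind such a result.** Expected deaths are 85 × 0.038 = 3.2, and P(3 or fewer) = 0.59. One death against two (extracorporeal vs in situ) meets the criterion with both tests. If later-randomised patients with 30-day data are also counted, the expected number rises, to at most 170 × 0.038 = 6.5.

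**6. A boundary that holds 2.5%.** O'Brien-Fleming-type spending at 50% information: 2 × [1 − Φ(2.2414 / 0.7071)] = 0.0015 one-sided. The final level that brings the total to 0.025 is 0.0245 (z = 1.969).

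**7. Timing.** {21b} names the primary endpoint and the 6-month assessment in one sentence, while {12} puts the primary endpoint at 30 days and 6-month mortality among the secondary outcomes. The gap is about five months. No part of the error in steps 2 and 3 comes from it.

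**The case against.** The strongest reply is that the article is silent rather than wrong. It does not say that the interim is tested at 0.05, boundaries are often kept in an analysis plan or DMC charter that is not shown, the DMC includes a statistician, and the output is a recommendation rather than a binding stop. This stands to the extent that nobody can say that no boundary exists, and that every error figure above is conditional on using the stated threshold. It does not dispose of the point: the article sets a flat P < 0.05 twice and spends all of the alpha on one analysis. An adjusted rule elsewhere would contradict both.

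Other parts of the reply also stand:

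- The tests named for categorical outcomes are chi-square and Fisher. A Fisher test for a difference could hardly succeed at about 3 deaths (3 of 43 vs 0 of 42 gives P = 0.24), so the early-success rates hold only for the non-inferiority test in {20c}.
- Success is required in both ITT and PP. This is not modelled and would lower the figures somewhat.

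A reader might infer that the 6-month timing itself inflates the error. It does not; it causes ambiguity and delay. A reader might also infer that an early stop would certainly rest on 3 deaths and forfeit half of the endoleak, re-intervention and 1-year data. The documents do not support that either: patients randomised during the wait would add events, and {21b} does not say that follow-up of enrolled patients would end.

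**Conclusion.** The point holds and should be corrected before the interim. As written, the article combines an efficacy look that can stop the trial, a single unadjusted threshold, and a sample size that leaves no alpha for that look. If P < 0.05 is applied at both looks, one-sided error is about 4.2% instead of 2.5% by normal theory. In the exact calculation it rises by about 1.3 to 1.5 points with a score test and by about 2.6 to 3.0 points with Wald. Under the planning rate of 3.8%, an early non-inferiority result is a likely event (41-51% score, 65-66% Wald) if only the 85 patients count.

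The mismatch between a 6-month trigger and a 30-day endpoint is a second, independent contradiction. It affects clarity and timeliness, not the error rate. Turning the efficacy look into a harm-only review is one option but a design preference; the documents do not make it necessary.

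**What to change.** 1. In {21b}, trigger the look when 85 patients have reached day 30, and name 30-day all-cause mortality as the endpoint tested.
2. State either an alpha-preserving boundary, for example O'Brien-Fleming-type spending with one-sided 0.0015 at 50% and 0.0245 at the end, or that no early non-inferiority claim will be made.
3. In {20a} and {20b}, replace the flat P < 0.05 for the primary test by these limits, and name the non-inferiority test. The choice matters: with this boundary, the exact two-look error is 2.2% for the score test but still 4.2-4.3% for Wald.
4. State that enrolled patients are followed to 1 year whatever the interim result.

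**Cost.** Protocol wording only. The chance of an early positive stop falls sharply (score test, 42 vs 42: from 41% to about 2%). The loss of final power is negligible by normal theory, because the final critical value moves only from 1.960 to 1.969. With 85 per arm and so few deaths, the exact score test steps from 83.9% (one look at 1.96) to 81.3%, because of discreteness.

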### Methods for additional analyses (e.g., subgroup analyses) {20b}

Two prespecified subgroup analyses of age (18–49 vs. 50–80) and gender will be conducted for the primary outcome by adding an interaction term (e.g., age × group) into the Cox regression model. A sensitivity analysis will be conducted for the primary outcome based on the per-protocol set, which included patients who adhered to the treatment and follow-ups. Continuous data will be compared using the Student *t*-test or Mann–Whitney *U* test for parametric and non-parametric data, respectively. Categorical data will be compared using the chi-square test or Fisher’s exact test, as appropriate. Since the participants might crossover or be lost to follow-up, non-inferiority will be tested using two analysis sets. One set is the intention-to-treat (ITT) set, which includes all patients as randomized, regardless of whether they received the assigned treatment. The other is the per-protocol (PP) set. *P* < 0.05 will be considered statistically significant, and all data will be analyzed using SAS 9.2 software.

### Methods in analysis to handle protocol non-adherence and any statistical methods to handle missing data {20c}

The primary outcome will be analyzed according to the modified intent-to-treat principle, which will minimally exclude patients without receiving the assigned treatment or with missing primary outcome data. We propose declaring extracorporeal fenestration non-inferior to in situ fenestration in patients with aortic disease involving the left subclavian artery, only if shown to be non-inferior using both the “intention-to-treat” and “per-protocol” analysis sets.

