## Data collection and management

### Plans for assessment and collection of outcomes {18a}

Baseline data will be collected after participants have signed informed consent. For the experimental group, intervention-related data will be obtained from the electronic medical records system within 30 days after patient discharge. Follow-up data will be obtained through outpatient visits or telephone interviews after the participants have completed each follow-up aortic CTA examination.

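### Sections {20b} and {20c} conflict on which analysis set decides the primary outcome: a modified ITT that drops non-receivers and missing outcomes, or an ITT of everyone randomized

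*Protocol article*

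**What the plan says.** Three statements in the protocol article bear on the set used for the primary outcome.

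- Section {20c}, on the analysis of the primary outcome: it follows a "modified intent-to-treat principle, which will minimally exclude patients without receiving the assigned treatment or with missing primary outcome data".
- Section {20b}, on the sets for the non-inferiority test: "One set is the intention-to-treat (ITT) set, which includes all patients as randomized, regardless of whether they received the assigned treatment". The second set is PP. The reason given for having two sets is that participants may cross over or be lost to follow-up.
- Section {20c}, immediately after the modified ITT sentence: extracorporeal fenestration is declared non-inferior "only if shown to be non-inferior using both the “intention-to-treat” and “per-protocol” analysis sets".

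Section {20b} also gives PP a second label: "A sensitivity analysis will be conducted for the primary outcome based on the per-protocol set, which included patients who adhered to the treatment and follow-ups".

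On data capture, section {18a} takes follow-up data from outpatient visits or telephone interviews "after the participants have completed each follow-up aortic CTA examination".

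**The concern.** The modified ITT appears once, as the set for the primary outcome. It is not mentioned in {20b}, is not named in the decision rule and is not reconciled with the ITT set. Two analysts following the text in good faith could therefore lock different primary sets.

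The choice matters because the modified ITT excludes patients for the two events that {20b} cites as the reason for testing two sets. If it stands in for ITT, patients leave the comparison because of what happened after randomization. The set then moves toward PP, and requiring both sets protects less against bias from crossover and loss. With a rare primary outcome, a handful of such exclusions is large relative to the number of deaths.

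Exclusion is also the only handling of a missing primary outcome that is stated, and it cannot be squared with a set of all patients as randomized.

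**Working it through.** **1. The definitions side by side**

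| Patient | Modified ITT, {20c} | ITT, {20b} | PP, {20b} |
|---|---|---|---|
| Received the assigned technique, day-30 status known, attended follow-ups | in | in | in |
| Received the assigned technique, day-30 status known, missed a follow-up | in | in | out, or unclear |
| Did not receive the assigned technique (crossover) | out | in | out |
| Day-30 status missing | out | in | out, if a follow-up was missed |

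The modified ITT and ITT columns differ in the last two rows. There the modified ITT agrees with PP. In the second row it does not, so the two sets are close but not the same.

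**2. The plan's own figures**

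Inputs from section {14}: 3.8% mortality in both arms, margin 10 points, two-sided alpha 0.05, beta 0.20, 77 per group, 170 in total (85 per arm at 1:1).

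- n = 2 × 0.038 × 0.962 / 0.10² × (1.960 + 1.282)² = 76.8, so 77 per group. This uses beta/2, as in an equivalence calculation. The formula as printed, with the beta quantile, gives 57.4, so 58. That is a separate matter.
- One-sided non-inferiority power at these inputs is 92.6% with 85 per arm and 90.1% with 77. Using the full ITT set leaves the sample size at 170, so power is not the issue here.
- Expected deaths: 85 × 0.038 = 3.23 per arm; 170 × 0.038 = 6.46 in total.

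**3. Where the margin is met or missed, with 3 deaths of 85 in the in situ arm**

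Wald upper limit = d + 1.96 × √[pA(1 − pA)/nA + pB(1 − pB)/nB], where A is extracorporeal, B is in situ and d = pA − pB. Newcombe limits and the score test serve as checks.

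| Deaths A v B | d (points) | Wald upper | Newcombe upper | 10-point margin |
|---|---|---|---|---|
| 4/85 v 3/85 | 1.2 | 7.15 | 8.3 | met |
| 5/85 v 3/85 | 2.4 | 8.7 | 9.9 | met (score one-sided p = 0.0249) |
| 6/85 v 3/85 | 3.5 | 10.2 | 11.4 | missed (score one-sided p = 0.0502) |

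**4. A scenario in which the set decides the result (assumed counts)**

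The documents give no crossover count and no mortality among crossovers. Suppose 6 of 85 die in group A and 3 of those 6 did not receive the assigned fenestration.

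- Full ITT, 6/85 v 3/85: d = 7.06 − 3.53 = 3.5 points; standard error √(0.000772 + 0.000401) = 0.0342; upper limit 3.53 + 6.71 = 10.2. Margin missed.
- Modified ITT, 3/82 v 3/85: d = 3.66 − 3.53 = 0.1 points; standard error √(0.000430 + 0.000401) = 0.0288; upper limit 0.13 + 5.65 = 5.8 (Newcombe 7.1). Margin met.

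**5. A milder scenario in which it does not**

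Suppose 5 of 85 cross over with 20% to 40% mortality and the other 80 have 3.8%. The full-ITT risk is (80 × 0.038 + 5 × 0.20)/85 = 4.75% to (80 × 0.038 + 5 × 0.40)/85 = 5.93%, about 4 to 5 deaths. Dropping the five returns it to 3.8%, a shift of 1.0 to 2.1 points. Against 3/85, both 4/85 and 5/85 meet the margin, and so does the reduced set, 3/80 v 3/85 (score z = −2.48). The estimate moves but the conclusion does not.

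**The case against.** The best defence is that the only sentences about the non-inferiority decision agree with each other. Section {20b} and the rule in {20c} both name ITT and PP, and ITT is defined in full. On that reading the modified ITT is a stray sentence, and its own wording promises that exclusions will be minimal. An analysis plan not shown here might settle it.

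Part of this stands. A reader might infer that the modified ITT removes the ITT half of the rule. The text does not go that far: it leaves that half undetermined. But the modified ITT sentence is explicit that it governs the primary outcome, so the conflict lies in what the article states and is not a detail left to another document.

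Four other stronger readings are tempting and are not supported:

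- *Deaths before the CTA become missing outcomes.* A recorded death is the outcome, not a missing one, and section {22} has a form for an event resulting in death sent to the chief investigator within 24 h. What remains is that {18a} ties follow-up contact to a completed CTA and describes the electronic-record route only for the experimental group. This is loose wording, not proof of informative missingness.
- *The modified ITT and PP are practically identical.* PP also requires adherence to follow-ups. Nor does the article say whether a failed attempt that was converted counts as not receiving the assigned treatment.
- *Seventeen patients (10% of 170) could be excluded.* The 10% in section {14} is a general dropout allowance in a trial with follow-up to 12 months. It does not estimate non-receipt or missing day-30 status.
- *One death decides the trial.* The step from 5 to 6 deaths is the edge of a rejection region, which any such test has. It is not produced by the modified ITT.

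Calling PP a sensitivity analysis is mainly a labelling fault, since the same section goes on to make it one of the two tested sets.

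**Conclusion.** The contradiction is real and should be resolved before analysis: the article gives two incompatible sets for the primary outcome. Following the stated exclusion would remove patients after randomization for reasons that may be related to outcome. The bias could run either way, depending on which arm loses more deaths.

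The size of the effect is conditional. With about 3 deaths expected per arm, three excluded deaths in one arm can reverse the conclusion (upper limit 10.2 v 5.8). That rests on assumed counts of 6 v 3 deaths, with half of the six in non-receivers. Five crossovers at 20% to 40% mortality shift the risk by 1.0 to 2.1 points and leave the conclusion unchanged. The sample size is unaffected.

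**What to change.** - In {20c}, replace the modified ITT sentence: the primary set is the ITT set of {20b}, all randomized patients by allocated group, with PP as the second required set. Delete the modified ITT or label it supplementary.
- Replace exclusion for a missing primary outcome with day-30 vital status obtained for every randomized patient in both groups, by telephone or hospital record, whether or not the CTA was done. Handle any residual missing status by a worst-case or tipping-point analysis, whose details can sit in the analysis plan.
- In {20b}, drop the word sensitivity for PP, so that it has one role.

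The cost is a change of wording and a little extra vital-status checking; section {18b} already has a researcher telephoning participants about follow-up. The estimate may come out slightly less favourable. No additional patients are needed.

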### Plans to give access to the full protocol, participant-level data, and statistical code {31c}

Upon reasonable request, the corresponding author will provide access to the full protocol, participant-level data, and statistical code.

## Oversight and monitoring

### Composition of the coordinating center and trial steering committee {5d}

The coordinating center for this clinical trial will be The Fourth Affiliated Hospital, Zhejiang University School of Medicine. We will develop a trial steering committee (TSC) responsible for providing strategic guidance, monitoring the progress of the trial, and making critical decisions related to the trial protocol and overseeing the overall conduct of the study. The TSC will consist of two independent experts in vascular surgery and one independent statistician.

### Composition of the data monitoring committee, its role and reporting structure {21a}

We will also develop a data monitoring committee (DMC) to independently monitor trial data, ensure participant safety, and maintain data integrity and quality throughout the study. The DMC will comprise surgeons, radiologists, and statistician. The DMC meeting will be held half a year.

### Adverse event reporting and harms {22}

An adverse event (AE) is an untoward medical occurrence in a patient or clinical study subject, which may or may not be caused by the investigational device. All such events, whether expected or not, should be recorded. A severe adverse event (SAE) is an untoward and unexpected medical occurrence or effect that results in death or is life-threatening, explicitly referring to an event in which the subject was at risk of death at the time of the event. It does not refer to an event that hypothetically might have caused death if it were more severe, requires hospitalization or prolongation of existing inpatients’ hospitalization, results in persistent or significant disability or incapacity, or results from a congenital anomaly or congenital disability. All AEs should be reported as following procedures.

An SAE form should be completed and sent by fax or email to the chief investigator within 24 h. All SAEs should be reported to the Research Ethical Committee; the event was “related” (i.e., resulted from the administration of any of the research procedures) and “unexpected” (i.e., an event that is not listed in the protocol as an expected occurrence). Reports of related and unexpected SAEs should be submitted within 15 days of the chief investigator’s awareness of the event, using the NRES SAE form for non-IMP studies. Investigators should report any SAEs as required by Research Ethics Committee, sponsor, and/or Research and Development Office.

The investigator and sponsor will do their best to prevent possible injury caused by the design of this study. In case of any injury related to this study, the sponsor will bear the corresponding treatment costs and make compensation by national laws and regulations. If an adverse event caused by the investigational compression treatment causes harm, the clinical research institution and the investigator will provide timely and adequate treatment and management according to the routine clinical treatment.

